## Abstract

**Background::**

Major depressive disorder is marked by high prevalence and elevated suicide risk. Modified electroconvulsive therapy (MECT) is a well-established, effective, and fast-acting method for treating major depressive disorder with acute suicide control, though its application is constrained by adverse effects. Enhancing the therapeutic effectiveness and/or reducing the adverse effects of MECT holds clinical practical value. Ascorbic acid (AA) can enhance the effectiveness of some antidepressants, yet its effects on depressed patients undergoing MECT lack clinical evidence. This study investigates whether AA augments the antidepressant effects of MECT in patients with major depressive disorder.

**Methods and Analysis::**

This is a prospective, randomized, double-blind, placebo-controlled trial. We will enroll 240 patients with major depressive disorder scheduled for MECT. Participants will be treated either with intravenous AA (500 mg, n = 120) or with intravenous normal saline (n = 120), administered immediately before each MECT session, just prior to induction of general anesthesia. The primary outcome is the treatment response rate, defined as the proportion of patients with a ≥50% reduction in the 24-item Hamilton Depression Rating Scale (HAMD-24) score. Secondary outcomes include remission rate, presence of psychotic symptoms, cognition, and adverse effects. This study is expected to provide an evidence based, safe, and cost effective strategy for optimizing MECT protocols, as well as potential directions for future mechanistic investigations.

**Ethics and Dissemination::**

The study will adhere to the principles of the Declaration of Helsinki. It received approval from the Institutional Review Board of the First Affiliated Hospital of Chongqing Medical University, China (Approval No. 2024-235-01). Written informed consent will be obtained from all participants. Results will be disseminated through peer reviewed publications and conference presentations. This study will offer the first clinical evidence of the effects of AA on patients diagnosed with major depressive disorder undergoing MECT. The findings may indicate the potential of AA for refining MECT based therapeutic strategies, optimizing depression treatment protocols, and improving clinical prognosis.

**Clinical Trial Registration::**

The study has been registered on https://www.chictr.org.cn/index.html (registration number: ChiCTR2500095678; registration link: https://www.chictr.org.cn/showproj.html?proj=248072).

## Main Points

1. Modified electroconvulsive therapy (MECT) remains an irreplaceable and essential antidepressant treatment to date, despite being limited by associated adverse effects. Further exploration into methodological refinements of MECT may yield additional clinical benefits for patients with depression.

2. This study is expected to establish the initial clinical evidence for the impact of ascorbic acid in patients diagnosed with major depressive disorder undergoing MECT.

3. Whether by enhancing the therapeutic efficacy of MECT and/or mitigating its adverse effects, the findings may suggest that ascorbic acid holds potential for refining MECT-based therapeutic strategies, optimizing depression treatment protocols, and improving clinical outcomes.

## 1. Introduction

Depression is a major global mental health challenge across all age groups, as reported by the World Health Organization [1]. Major depressive disorder represents a leading cause of both mental and physical disability and ranks as a primary factor in the global disease burden [2,3]. Modified electroconvulsive therapy (MECT) is a rapid-acting and highly effective first-line intervention indicated for severe conditions of major depressive disorder, including treatment-resistant depressive episodes, and especially for the acute control of suicidal ideation [4,5]. It has been extensively incorporated into evidence-based treatment algorithms for severe major depressive disorder in contemporary clinical practice [6]. MECT under general anesthesia represents a substantial advancement over conventional electroconvulsive therapy by preventing physical injuries such as fractures, muscle strains, and bite wounds that result from generalized convulsions. However, MECT still carries adverse effects, including cognitive impairment (e.g., learning and memory deficits) and myalgia, which often elicit patient fear and poor treatment compliance [7]. Beyond modifications pertaining to the co-administration of general anesthesia and medications, improvements in the electroconvulsive parameters and conditions have been explored; the use of nonconvulsive electrotherapy and transnasal humidified rapid-insufflation ventilatory exchange during MECT is designed to enhance therapeutic effectiveness and/or mitigate adverse effects [7,8,9,10]. Further refinements in MECT treatment are likely to yield additional benefits for patients.

Ascorbic acid (AA) is an essential vitamin and a key antioxidant for humans [11]. Beyond its antioxidant properties, AA possesses supplementary advantages including a favorable safety profile, easy accessibility, high public acceptance, and good medication adherence. It has been recognized as a neuromodulator involved in many critical processes within the central nervous system [12,13]. AA is no longer regarded as a simple antioxidant, but rather an active molecule that exerts antidepressant effects through the integration of multiple pathways such as antioxidant, anti-inflammation, neurotransmitter regulation, and neurotrophic support [14,15,16,17,18,19]. The potential role of AA in mood regulation, as well as in the pathogenesis and treatment of depression, has garnered increasing attention. Evidence has suggested that AA exerts its effects through multiple pathways and targets. First, AA mitigates oxidative neuronal damage by directly neutralizing reactive oxygen species, inhibiting lipid peroxidation, and regenerating other antioxidants [14,15]. Its antidepressant effects are closely linked to modulation of glutathione synthesis and inhibition of NOD-like receptor family pyrin domain containing 3 (NLRP3) inflammasome activation, thereby reducing the maturation and release of pro-inflammatory cytokines like interleukin-1β and interleukin-18 [16]. Second, AA also serves as an essential cofactor in the biosynthesis of monoamine neurotransmitters, participating in the production of norepinephrine and neuropeptides, thus contributing to emotional regulation [16]. Third, AA modulates synaptic plasticity by regulating glutamate receptor function and influencing long-term potentiation, promotes the expression of brain-derived neurotrophic factor (BDNF), a key protein for neuronal survival and synaptic plasticity, and reverses the suppression of BDNF-related signaling pathways in animal models of depression [15,16,17,18]. Fourth, recent research has highlighted the gut–brain axis as a novel pathway for the mood-regulating effects of AA, with findings indicating that AA supplementation alters gut microbiota composition, leading to decreased serum lipopolysaccharide levels, attenuated systemic inflammation, elevated serum BDNF, and enhanced mental vitality in healthy adults [19]. Last, both preclinical and clinical evidence have supported the antidepressant potential of AA, including reversing chronic stress-induced depression-like behaviors in animal models [14,15], and enhancing the efficacy of selective serotonin reuptake inhibitors in patients with major depressive disorder [14,16].

The theoretical foundation of this study is rooted in the central role of oxidative stress in the pathogenesis of depression. A substantial body of evidence has demonstrated that major depressive disorder is closely associated with a significant imbalance between oxidant and antioxidant systems, characterized by increased generation of reactive oxygen species, elevated lipid peroxidation (e.g., increased malondialdehyde levels), oxidative damage to DNA and proteins, and dysfunction of endogenous antioxidant defense mechanisms such as superoxide dismutase [20,21]. This pathological state not only directly induces neuronal injury but also triggers neuroinflammatory responses, disrupts the metabolism and signaling of monoamine neurotransmitters, and impairs synaptic plasticity, thereby collectively constituting a fundamental pathophysiological basis of depression [20]. Notably, MECT may itself provoke transient oxidative stress responses during the induction of seizures and the administration of general anesthesia, and regulate downstream targets of synaptic plasticity in multiple brain regions [20,21,22].

AA exerts a certain degree of antidepressant effects and improves mood [23]. Literature suggests the potential involvement of oxidative stress in the pathophysiological mechanisms of depression, as evidenced by reduced plasma AA levels and elevated oxidative stress markers in patients [20,24,25]. Therefore, the mechanisms underlying the effects of MECT potentially involve the intricate participation and interplay of oxidative stress, with antioxidant interventions representing a promising therapeutic adjunct [26,27].

Research findings have indicated that AA alone has limited antidepressant efficacy but can assist in other antidepressant treatments. In preclinical studies, administration of AA ameliorated depression-like behaviors and reversed associated pathological neural alterations in mice [28,29]. Co-administration of AA with ketamine or its enantiomer (e.g., esketamine, a recently approved new rapid-acting antidepressant) significantly enhanced antidepressant efficacy, reduced psychotomimetic-like side effects, and potentially allows for lower ketamine dosing, thereby improving treatment tolerability in animal models [30,31]. Another clinical study further demonstrated that adjunctive use of AA during fluoxetine therapy for pediatric major depressive disorder resulted in a marked decrease in depressive symptoms, with no significant adverse effects observed [32]. To date, however, there have been no reported studies on the use of AA in the course of MECT.

Based on the current evidence, we hypothesize that adjunctive AA administration during MECT will enhance antidepressant effects and may even directly alleviate the adverse effects of MECT. However, direct clinical evidence derived from well-designed randomized controlled trials remains lacking. Therefore, this study will address these evidence gaps by conducting a prospective, randomized controlled trial to evaluate the clinical effectiveness of AA augmentation in individuals with major depressive disorder undergoing MECT, with a priority focus on confirming treatment response.

## 2. Materials and Methods

### 2.1 Study Design and Ethics

This study is a prospective, randomized, double-blind, placebo-controlled, parallel-group clinical trial designed to assess the effect of AA treatment on the therapeutic outcomes and tolerability of MECT in patients with major depressive disorder. The protocol was drafted according to the Standard Protocol Items: Recommendations for Interventional Trials (SPIRIT), and was registered at the Chinese Clinical Trial Registry (Registration No. ChiCTR2500095678) on January 10, 2025. Fig. 1 illustrates the participant flow throughout the study.

**Fig. 1. F001:**
[figure not shown]
**Study design**. Abbreviations: AA, ascorbic acid.

### 2.2 Participants

Potential participants will be screened at the Department of Psychiatry in the First Affiliated Hospital of Chongqing Medical University. Eligible participants will be enrolled after providing written informed consent and may withdraw from the study at any point.

Inclusion Criteria: (1) Diagnostic and Statistical Manual of Mental Disorders, Fifth Edition (DSM-5) diagnosis of major depressive disorder requiring MECT and hospitalization; (2) aged 18–59 years; (3) body mass index (BMI) between 18.5–30 kg/m^2^; (4) physical status (American Society of Anesthesiologists, ASA) I–II, without major comorbidities; (5) willingness of the patients and/or their legal guardian to offer written informed consent.

Exclusion Criteria: (1) comorbid with severe medical and/or surgical diseases, including significant cardiovascular or cerebrovascular diseases, uncontrolled hypertension, elevated intracranial pressure, or the presence of cardiac pacemakers or intracranial implants; (2) co-occurring psychiatric disorders (e.g., schizophrenia); (3) conditions that may interfere with efficacy assessments (e.g., catatonia (diagnosed by experienced psychiatrists according to DSM-5 criteria), cognitive impairment, illiteracy, or intellectual disability); (4) contraindications to anesthesia or MECT (e.g., full stomach, severe pulmonary dysfunction, known allergy to anesthetics); (5) known allergy to ascorbic acid or any contraindications to its administration; (6) history of alcohol or other substance dependence; (7) previous ineffectiveness or serious adverse effects of MECT; (8) pregnancy; (9) participation in another clinical trial within the past year.

Participants will be discontinued from the study if any of the following occur: (1) serious adverse effect necessitating termination of the intervention; (2) request by the patient and/or family to withdraw; (3) clinical circumstances evaluated by the treating psychiatrist that warrant discontinuation of MECT (e.g., remission according to the 24-item Hamilton Depression Rating Scale (HAMD-24) criteria, defined as a score of <10 on two consecutive assessments, occurrence of severe cognitive impairment, intolerable reactions, or no clinical improvement after eight MECT sessions, etc.); (4) violation of trial protocol.

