### 2.6 Outcomes

Outcome categories and their assessment timepoints are detailed in Table 1. Data will be collected by independent investigators who are blind to group allocation and intervention assignments.

**Table 1. T001:** **Outcome measurements**.

Outcomes	Measurements	Scheduled time		
		Baseline	Each MECT	Before discharge
Primary outcome:				
Treatment response rate	HAMD-24 scale	×		×
Secondary outcomes:				
Depression remission rate	HAMD-24 scale	×		×
Suicide ideation remission rate	HAMD-24 scale (item 3)	×		×
Associated psychotic symptoms	BPRS scale	×		×
Cognition	MoCA scale	×		×
Electroconvulsive parameters	Field recording		×	
Anesthesia related data	Field recording		×	
Blood biomarkers	Blood detection	×		×
Safety outcomes:				
Adverse effects of ascorbic acid	Observation and inquiry		×	×
Adverse effects of MECT	Observation and inquiry		×	×

BPRS, Brief Psychiatric Rating Scale; HAMD-24, 224-item Hamilton Depression Rating Scale; MECT, modified electroconvulsive therapy; MoCA, Montreal Cognitive Assessment; "×" symbol indicates the time point at which each assessment is carried out.

For the confirmatory index, the primary outcome is the treatment response rate of the group. Response is operationally defined as achieving at least a 50% reduction from baseline on the HAMD-24 total score by the end of treatment [37]. A qualified psychiatrist rates the 24 items of the HAMD-24 on a 0–4 severity scale (0 = none, 1 = mild, 2 = moderate, 3 = severe, 4 = very severe) of 24 items [37]. Treatment response rate is expressed as the percentage of patients responding to MECT relative to the total number of patients in each group. The rationale for selecting the “response rate” as the primary outcome is as follows: (1) the response to an antidepressant treatment with a ≥50% reduction in the scale score has been generally recognized as a clinically meaningful treatment success intuitively reflecting the efficacy intensity of the intervention measures in confirmatory studies [38,39]; and (2) is an internationally accepted consensus standard for antidepressant efficacy evaluation by the US Food and Drug Administration (FDA) and European Medicines Agency (EMA) [40,41], and has been widely used as the primary outcome in evaluating the efficacy of MECT as well [42,43].

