### 2.7 Sample-Size Estimation

The primary outcome is the response rate of the group to MECT. As no prior data exist regarding the efficacy of AA augmentation in individuals diagnosed with major depressive disorder receiving MECT, the required sample size was determined based on our pilot study (*n *= 40, i.e., 20/gp) conducted over 6 mo, which indicated a response rate of 60% (12/20) in the placebo group and an improvement of 20% (16/20) in the AA group. With a two-sided α of 0.05, a power of 85% (1-β = 0.85), and 1:1 allocation, the calculation performed with PASS software (version 2021, NCSS, LLC, Kaysville, UT, USA) indicated a requirement of 93 participants/gp. To allow for an anticipated 22.5% attrition rate, a target enrollment of 120 participants/gp is planned, resulting in a final total sample of 240 subjects.

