### 2.8 Statistical Analysis

The intention-to-treat (ITT) analysis set in this study will include all randomly assigned participants, regardless of whether they received MECT treatment or completed the follow-up assessments. Analyses will be conducted using SPSS (version 26, IBM Corp., Armonk, NY, USA). Missing outcome or covariate data, including those from participants in the ITT set without post-baseline data, will be handled using multiple imputation, and a mixed model for repeated measures (MMRM) will be used where appropriate. For the primary outcome (the rate of response to MECT), binary logistic regression, with treatment group as the independent variable and pre-specified stratification factors included as covariates, will serve as the primary analytical method, and results will include an adjusted odds ratio (aOR) with a 95% confidence interval. Additionally, potential interaction effects between the stratification factors (age, sex, baseline HAMD-24 score) and the treatment group will be explored within this model for the primary outcome. The Chi-square test will be used as a supplementary analysis. Categorical variables, expressed as counts (percentages), will be compared between groups using the Chi-square test (or the Fisher’s exact test). Continuous variables will be presented as mean (standard deviation) (if normally distributed) or median (interquartile range) (if non-normally distributed), and compared using *t*-test or nonparametric tests (e.g., Mann-Whitney U test), as appropriate. For secondary-outcome analyses, logistic regression will be performed to adjust for potential confounders. For multiple comparisons, the Bonferroni correction will be applied for the secondary and exploratory outcomes. Specifically, the Bonferroni correction will be applied uniformly across all pre-specified secondary outcomes to control the family-wise error rate. We acknowledge that this is a conservative approach, which prioritizes the control of Type I error over statistical power for these outcomes. Given their exploratory feature, between-group differences in blood biomarker levels from baseline to post-treatment will be compared using an analysis of covariance (ANCOVA) adjusted for baseline values, and the Benjamini–Hochberg false discovery rate (FDR) procedure will be applied to correct for multiple testing. Pre-specified subgroup analyses will be conducted based on age (<45 and ≥45 years), sex (male and female), and baseline HAMD-24 score (divided at the median). These analyses will be performed by including an interaction term between the treatment group and the subgroup variable in the primary statistical model (binary logistic regression). Given the exploratory and hypothesis-generating nature of these subgroup analyses, no multiplicity adjustment will be applied to the interaction tests, and the results will be interpreted with caution. Sensitivity analyses will include the per-protocol (PP) analysis and complete-case analysis, an evaluation using alternative missing-data-handling strategies, and re-analyses excluding specific populations (e.g., protocol violators) to assess the robustness of the findings. All hypothesis tests will be two-tailed, and a statistical significance level will be set at* p *< 0.05.

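### Section 2.2 merges stopping MECT with leaving the study, and nothing secures the final HAMD-24 for patients who stop because they remitted or did not improve

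*Protocol article*

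**What the plan says.** All references are to the protocol article.

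- **Section 2.2, discontinuation.** The lead-in is "Participants will be discontinued from the study if any of the following occur". The third item concerns circumstances in which the psychiatrist judges that MECT should stop. Its examples include "remission according to the 24-item Hamilton Depression Rating Scale (HAMD-24) criteria, defined as a score of <10 on two consecutive assessments" and "no clinical improvement after eight MECT sessions". The fourth item is "violation of trial protocol".
- **Section 2.6, primary outcome.** Response is "at least a 50% reduction from baseline on the HAMD-24 total score by the end of treatment". Table 1 marks the HAMD-24 at baseline and before discharge only. Its column for each MECT session is empty for this scale, and there is no early-termination visit.
- **Section 2.6, remission.** This secondary outcome uses the same cut-off (below 10, reached twice in sequence) as the discontinuation criterion, with everyone in the group as denominator.
- **Section 2.7.** "To allow for an anticipated 22.5% attrition rate", the target is raised from 93 to 120 per group.
- **Section 2.8.** The ITT set is everyone randomised. "Missing outcome or covariate data, including those from participants in the ITT set without post-baseline data, will be handled using multiple imputation", with a mixed model for repeated measures where appropriate. Sensitivity analyses are per-protocol, complete-case, other ways of handling missing data (not specified), and re-analyses leaving out groups such as protocol violators.

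No section says whether a discontinued patient keeps or loses the final HAMD-24.

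**The concern.** The third item gives reasons to stop a treatment, but the lead-in applies them to study participation. Two of these reasons, remission and lack of improvement, are close to being the outcome itself. A patient who has scored at most 9 has at least halved any baseline of 18 or more, and a patient without improvement is a non-responder.

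If such patients leave before the one scheduled post-baseline rating, their response status is missing because of what it is. Standard multiple imputation assumes that missingness is explained by the observed data. With no interim HAMD-24 in the schedule, there would be little to support that assumption. Later analysis cannot recover a rating that was never made.

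Protocol violation is a separate matter. It is not an outcome-driven reason, but removing violators from the study gives up ratings that an ITT analysis should use. The planned re-analysis without violators makes sense only if they are in the main data.

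**Working it through.** **1. The plan's own figures.** Inputs from section 2.7: 60% vs 80% response, two-sided α 0.05, power 85%, 1:1 allocation.

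n = [1.960·√(2·0.70·0.30) + 1.036·√(0.60·0.40 + 0.80·0.20)]² / 0.20² = (1.270 + 0.655)² / 0.04 ≈ 92.7, so 93 per group. Then 93/(1 − 0.225) = 120. Both stated figures reproduce. Power is 85.1% at 93 per group and 92.7% at 120 per group with nobody lost. The planned odds ratio (OR) is (0.80/0.20)/(0.60/0.40) = 2.67.

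**2. The attrition allowance.** 0.225 × 120 = 27 patients per group. At the mean planned response of 70%, remitters alone use this up once 0.225/0.70 = 32% of responders remit and are counted as lost.

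**3. What literal removal does to the odds ratio.** In an arm with true response p, let r be the share of responders who leave unrated as remitters and s the share of non-responders who leave unrated for lack of improvement. Response among those left is

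p(1 − r) / [p(1 − r) + (1 − p)(1 − s)].

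The OR among those left is therefore

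2.67 × (1 − r_AA)/(1 − r_placebo) × (1 − s_placebo)/(1 − s_AA).

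Imputation within arm from baseline data would roughly reproduce these rates. The documents give neither r nor s, so all values below are assumptions. Power is for a two-proportion test on the rated patients, starting from 120 per group.

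| r placebo / AA | s placebo / AA | Observed response | OR | Missing (mean) | Power |
|---|---|---|---|---|---|
| 0 / 0 | 0 / 0 | 60.0% vs 80.0% | 2.67 | 0% | 93% |
| 0 / 0 | 0.50 / 0.50 | 75.0% vs 88.9% | 2.67 | 15% | 74% |
| 0.50 / 0.50 | 0.25 / 0.25 | 50.0% vs 72.7% | 2.67 | 42.5% | 79% |
| 0.50 / 0.50 | 0.50 / 0.50 | 60.0% vs 80.0% | 2.67 | 50% | 67% |
| 0.50 / 0.60 | 0.25 / 0.25 | 50.0% vs 68.1% | 2.13 | 46.5% | 54% |
| 0.40 / 0.60 | 0.30 / 0.30 | 56.3% vs 69.6% | 1.78 | 45% | 34% |

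**4. One example in full.** Assume that 40% of all placebo patients and 60% of all AA patients remit and leave unrated, and that nobody else leaves.

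- Placebo: (0.60 − 0.40)/(1 − 0.40) = 33.3% of 72 patients.
- AA: (0.80 − 0.60)/(1 − 0.60) = 50.0% of 48 patients.
- OR = (0.50/0.50)/(0.333/0.667) = 2.00. By the formula, r is 0.40/0.60 = 0.667 and 0.60/0.80 = 0.75, and 2.67 × 0.25/0.333 = 2.00.
- Power: the pooled rate is 48/120 = 0.40. The null SE is √[0.24(1/72 + 1/48)] = 0.0913 and the alternative SE is √(0.2222/72 + 0.25/48) = 0.0911. Then (0.1667 − 1.96 × 0.0913)/0.0911 = −0.13, so power is about 45%.
- Losses are 48 and 72 patients, against the 27 allowed per group.

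**The case against.** The strongest reply is that these patients are meant to be rated.

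- The number of MECT sessions is not fixed, so remission or failure is a usual way for a course to end. End of treatment can be read as the moment MECT stops.
- The patients are in hospital, so the rating before discharge is still available.
- The remission rate in section 2.6 could not be calculated if remitters left unrated. A remitter has by then been scored below 10 twice, so response is normally known.
- The imputation model is properly left to an analysis plan that is not shown, and section 2.8 does not restrict it to baseline variables.

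Most of this stands, and it shows what the protocol probably intends. It does not remove the conflict, because section 2.2 says the opposite and no sentence secures the rating. The two successive scores below 10 also need HAMD-24 ratings that Table 1 does not schedule, so it is not assured that they enter the trial data.

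A reader might infer three stronger points that the documents do not support:

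- **That missing-at-random fails by design.** It fails only if section 2.2 is applied literally.
- **That the primary odds ratio and every sensitivity analysis are biased.** With equal removal shares in both arms the odds ratio stays at 2.67. In the 75.0% vs 88.9% row only the risk difference shrinks, and that is not the primary measure. The alternative missing-data analyses are unspecified, so they cannot be called biased.
- **That protocol violators drop out of the ITT set.** Section 2.8 keeps everyone randomised. What would be lost is their ratings.

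**Conclusion.** The concern holds as a conflict in the text with a conditional consequence. Section 2.2 sends patients out of the study for reasons that only justify stopping MECT, and for protocol violation. The remission denominator in section 2.6 and the ITT set in section 2.8 imply that they are still rated. The passages must be reconciled.

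If section 2.2 is followed literally, response is missing for outcome-related reasons, the planned imputation lacks a credible basis, and the allowance of 27 per group is spent once 27 patients in a group remit. The effect on the odds ratio depends on how removal differs between arms. There is no change under equal shares, although power still falls. There is attenuation if AA raises the share of responders who remit, for example to 2.00 with about 45% power under assumed remission of 40% vs 60%. These shares are assumptions, and every such figure supposes that all patients who leave go unrated. If all are rated, the planned contrast is kept with about 93% power at 120 per group.

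**What to change.** Leave the clinical stopping criteria as they are and change what they trigger:

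1. In section 2.2, separate stopping study treatment from leaving the study.
2. State that every randomised patient who has not withdrawn consent has the planned end-of-treatment HAMD-24, BPRS and MoCA rated when MECT stops, whatever the reason, and that this rating is used in the ITT analysis. Align Table 1 with this.
3. Do not remove protocol violators from the study. Keep them in follow-up and in the ITT set, and exclude them only in the planned per-protocol and sensitivity analyses.
4. Reserve multiple imputation for ratings that truly cannot be obtained.
5. Reconcile the remission rule, which needs two successive HAMD-24 scores, with Table 1, which schedules one after baseline.

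The cost is a few sentences of protocol wording. The rating is already planned for these inpatients and would be made when MECT stops. No patients are added.
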